### Data collection method

The study will employ a two-phase mixed-methods implementation research design. Phase 1 will adopt a concurrent mixed-methods approach, in which quantitative and qualitative data will be collected simultaneously to comprehensively assess functional decline, quality of life, health conditions, healthcare utilisation, and socio-cultural determinants among middle-aged and elderly tribal populations in Jharkhand. The quantitative and qualitative findings will be analysed independently and integrated during interpretation to provide a comprehensive understanding of the community’s health needs. The integrated findings from Phase 1 will be used to identify, prioritise, and confirm the key domains that will underpin the development of the healthcare model in Phase 2. Building on these empirically derived domains, Phase 2 will focus on the co-development of a culturally sensitive, community-based integrated healthcare model through evidence synthesis and stakeholder consultation. This iterative process ensures that the proposed model is evidence-based, context-specific, and responsive to the health priorities, cultural practices, and service needs of tribal [8].

#### Quantitative component.

For the quantitative survey, villages from 5 blocks in East Singhbhum, Jharkhand, will be selected using multi-stage stratified random sampling to ensure representativeness of the tribal population. Within each selected village, eligible participants will be selected using random or systematic sampling methods, depending on feasibility (e.g., household listing followed by every nth household). The target population will include both middle-aged (45–59 years) and elderly (60 years and above) individuals. Data will be collected using structured questionnaires covering socio-demographic details, chronic disease profile, functional & nutritional status (e.g., Barthel’s Index, Lawton’s IADL, Long MNA), and quality of life (WHOQOL-BREF), and relevant clinical assessments, will be used to ensure consistency and reliability of data collection.

#### Qualitative component.

For the qualitative inquiry, convenient sampling will be employed to ensure diversity and representation across different age groups, genders, and tribal sub-communities. In-depth Interviews (IDIs), Focus Group Discussions (FGDs), and Key Informant Interviews (KIIs) will be conducted. Key stakeholders will include:

Community members across age categories (middle-aged and elderly).Gender-specific groups to capture differences in health-seeking behaviour and caregiving roles.Community leaders and traditional healers to understand cultural perspectives and indigenous practices related to aging and health.Frontline health workers (ASHA, ANM, AWW’s etc.) Government officials and healthcare providers to explore perspectives on service delivery, challenges, and integration with government programs like NPHCE.

The qualitative tools will explore lived experiences of aging, perceptions of functional decline, caregiving dynamics, health system access, and acceptance of community-based healthcare interventions.

### Integration of the findings

The integration of quantitative and qualitative findings is a key component of the concurrent mixed-methods design. Both data strands will be collected simultaneously, analysed independently, and integrated during interpretation to provide a comprehensive and culturally sensitive understanding of the health needs of tribal populations.

**Integration at the Interpretation Stage**

The two data strands will first be analysed independently. Quantitative findings will provide measurable estimates and patterns of functional decline, chronic conditions, and quality of life, while qualitative findings will provide contextual insights into the underlying cultural, social, and healthcare-related factors, including perceptions of ageing, healthcare access, and traditional health practices. Integration of the findings will enable comparison and triangulation across methods and support development of an evidence-informed, context-sensitive model.

**Domain Identification**

The integrated Phase 1 findings will inform the identification and confirmation of the key domains for the healthcare model. Quantitative patterns, such as areas of functional limitation, will be considered alongside qualitative findings on service gaps and socio-cultural factors. This combined evidence will help identify and prioritize the health needs and service gaps that the intervention should address within the tribal context of East Singhbhum.

**Evidence-Based Model Refinement**

The integrated findings will inform the development of the draft healthcare model, which will subsequently be refined through consultations with stakeholders (tribal elders, ASHAs, ANMs, NGO/Government authorities, public health experts). For example, gender-specific patterns identified quantitatively will be considered alongside qualitative insights into caregiving roles and health-seeking practices to inform the development of context-specific interventions. Similarly, findings on morbidity and healthcare needs will be considered alongside information on traditional healing practices to promote culturally appropriate integration of healthcare services.

Overall, quantitative findings will establish the magnitude and distribution of identified health needs, while qualitative findings will provide contextual understanding to guide how these needs can be addressed within the cultural and health-system context of tribal communities.

### Data collection procedure

The data collection for the mixed-method study will begin by obtaining necessary approvals from the Institutional Ethics Committee (IEC), Institutional Scientific Committee (ISC), and administrative permissions from the State Tribal Welfare Department, District Health Authorities, and Panchayat-level leaders in the selected districts. Community sensitization meetings will be held in each selected village to inform local leaders, ASHA workers, and residents about the study’s purpose and procedures, thereby building trust and encouraging participation. A household listing will be conducted to identify eligible individuals aged 45 years and above, including both middle-aged (45–59 years) and elderly (60 + years) participants. Informed consent will be obtained, and for illiterate participants, thumb impressions will be taken in the presence of a witness to ensure ethical participation.

### Expected outcome

#### Primary outcome.

Functional Decline: Assessment of loss of capacity to perform basic and instrumental activities of daily living among middle-aged and elderly tribal individuals.Quality of Life (QoL): Assessment of physical, psychological, social, and environmental well-being.Health and Morbidity Profile: Assessment of prevalent chronic conditions, such as hypertension and diabetes, and associated risk factors at baseline.Model Effectiveness: Assessment of short-term changes in mobility, ADL performance, self-rated health, and QoL following pilot implementation.

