**Expected Outcomes:**

The study will establish critical baseline data on tribal aging and develop a validated, scalable healthcare model. Expected results include improved health service utilization, early detection of functional decline, and policy-level impact on geriatric and tribal health strategies in India.

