### Secondary objective

#### Phase 2- Healthcare model development.

3. To design a community-based, culturally sensitive healthcare model to assess its feasibility and acceptability in improving functional ability and Quality of life across middle-aged and elderly tribal populations across all the blocks of East Singhbhum.

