**Healthcare Delivery System**	**Primary:** ASHAs, ANMs, and volunteers for screening and home visits. **Secondary:** CHCs/District Hospitals with dedicated geriatric/NCD clinics. **Tertiary:** Referral links to medical colleges.	Establishes a **structured referral and monitoring pathway** customized for the tribal landscape.
**Integration with Existing Programs**	Leverages **NPHCE, NPCDCS, NHM**, and national nutrition programs such as **ICDS and Poshan Abhiyan**.	**Unique Feature:** Provides programmatic convergence customized for tribal/elderly needs, which is rarely done systematically in existing models.
**Traditional Healing Practices**	Recognizes and documents traditional healers; promotes safe, evidence-based practices while discouraging harmful ones.	**Unique Feature:** Structured collaborative engagement with traditional healers to improve the community’s trust and acceptability of modern healthcare.
**Nutritional Practices**	Incorporates **tribal diets** and local food diversity; introduces low-cost, culturally acceptable interventions like kitchen gardens.	**Unique Feature:** Blends nutrition security directly with healthcare delivery rather than treating them as separate entities.
**Elderly-Focused Interventions**	Builds on NPHCE but is adapted for tribal settings, including **functional decline (ADL/IADL)** and quality of life assessments	**Unique Feature:** Adds community-based care models that specifically account for caregiver burden, social isolation, and financial dependence.

**Table 4 pone.0358356.t004:** Representing outcome measures and assessment timeline.

S.No.	Timeline	Outcome Components	Measurement Tools & Methods
1.	Phase1: Needs Assessment (Completion by November 2026	Baseline Functional Status, QoL, and Morbidity	• Barthel’s Index (for ADL) and Lawton’s Scale (for IADL). • WHOQOL-BREF questionnaire for Quality of Life. • Long MNA (Mini Nutritional Assessment) for nutritional status.
2.	Phase1: Qualitative Inquiry (Concurrent with quantitative)	Cultural Beliefs and Stakeholder Engagement	• In-Depth Interviews (IDIs), Focus Group Discussions (FGDs), and Key Informant Interviews (KIIs) with leaders, healers, and health workers.
3.	Phase 2: Model Implementation (June – August 2027)	Short-term Model Effectiveness	• Pre-post measures of functional ability and quality of life using the Phase 1 quantitative tools.

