
#### Phase 2: Development of the community -based healthcare model.

Objective 3. To design a community-based, culturally sensitive healthcare model to assess its feasibility and acceptability in improving functional ability and Quality of life across middle-aged and elderly tribal populations across all the blocks of East Singhbhum.

Phase 2 will build on the integrated quantitative and qualitative findings from Phase 1 to fulfil Objective 3, which involves developing a culturally appropriate, community-based integrated healthcare model for healthy aging among tribal populations. The identified domains from Phase 1 will be refined through stakeholder consultations involving tribal community representatives, Medical Officers, traditional healers, local leaders, public health experts, and other relevant stakeholders. Support from ASHA/Sahiya workers and local community stakeholders will be sought throughout participant mobilisation, community engagement, and implementation of the healthcare model Fig 3. Based on the consensus generated, the healthcare model will be developed and implemented in a selected village to assess its effectiveness, feasibility, and community acceptability. Written informed consent will be obtained from all participants prior to their involvement, either through signature or thumb impression.

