**Step 3: Implementation.**

### Assessment of the effectiveness of the model

The finalised model will then be implemented in a selected village, incorporating components such as health checkup, nutrition support, physical and mental health interventions, and home-based care. Further the effectiveness of the model will be evaluated using pre-post measures of functional ability and quality of life.

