#### Secondary outcomes.

Community Profiling: Mapping health determinants and identifying cultural beliefs or barriers to health-seeking behavior.Feasibility and Acceptability: Assessing how well the community-based integrated healthcare model is accepted by tribal residents and stakeholders.Healthcare Service Utilization: Measuring the community participation in health screenings and formal referral systems.Assessment of the feasibility, acceptability, and potential for wider implementation of the HOR-SATHI Healthy Ageing model in tribal communities.Institutional and Policy Impact: Long-term goals include the institutional adoption of the model by state health departments and providing evidence-based inputs for national geriatric and tribal health policies.

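### Model effectiveness is ranked as a primary outcome, but its objective is secondary and concerns feasibility, and a one-village pre-post comparison cannot attribute change to the model

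*Protocol article*

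**What the plan says.** **Objectives.** The primary objective is the Phase 1 needs assessment: functional decline, health conditions, risk factors and quality of life. The model appears only under the secondary objective (objective 3): "To design a community-based, culturally sensitive healthcare model to assess its feasibility and acceptability in improving functional ability and Quality of life". The abstract's Objectives paragraph likewise confines Phase 2 to designing the model and evaluating feasibility and acceptability.

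**Outcomes.** Under Expected outcome, the primary list has four items. Three match Phase 1. The fourth is "Model Effectiveness: Assessment of short-term changes in mobility, ADL performance, self-rated health, and QoL following pilot implementation". The secondary list contains "Feasibility and Acceptability: Assessing how well the community-based integrated healthcare model is accepted by tribal residents and stakeholders".

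**Evaluation design.** The Phase 2 section states that "the healthcare model will be developed and implemented in a selected village to assess its effectiveness, feasibility, and community acceptability". The section on assessing effectiveness adds: "Further the effectiveness of the model will be evaluated using pre-post measures of functional ability and quality of life". Table 4, row 3, under short-term model effectiveness and dated June to August 2027, gives "Pre-post measures of functional ability and quality of life using the Phase 1 quantitative tools". The Phase 2 timeline has the same three months and again one selected village. No comparator village or group, randomisation or repeated pre-intervention measurement is described.

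**Claim.** The abstract's Expected Outcomes says the study will "develop a validated, scalable healthcare model".

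**The concern.** Two problems meet in one item.

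The first is rank. A primary outcome sits under a secondary objective that names something else, while the outcomes that objective does name are ranked below it. A reader of the final report could not tell which Phase 2 result the study stands on.

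The second is attribution. The word effectiveness asserts that the model caused the change. With one village measured before and after, the model and everything else that happens in that village over the same period are the same contrast. An analysis plan written later cannot separate them, because the design supplies no information with which to do so. At stake is whether a favourable pilot result is read as evidence that the model works and can be scaled, when the design can show feasibility, acceptability and a descriptive change.

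**Working it through.** **1. The plan's own sample size.** Inputs from Sample size, Quantitative component: p = 0.343, d = 0.05, z = 1.96, design effect 1.5.

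n = 1.96² × 0.343 × 0.657 / 0.05² = 346.27, stated as 346. Then 346 × 1.5 = 519, rounded to 520. The figure reproduces. It sizes the precision of a Phase 1 prevalence. It does not size a change score, and no number is given for the pilot.

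**2. What the pilot could detect, for assumed numbers.** The average Phase 1 sample per village is 520/25 = 20.8, about 21. This is only an average, since allocation is proportionate, and the pilot need not be restricted to Phase 1 respondents. So a range is shown.

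Detectable mean change, in SDs of the change score, two-sided 5%, 80% power: (1.96 + 0.842)/√m.

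| People measured twice (assumed) | Detectable change |
|---|---|
| 21 | 2.802/4.583 = 0.61 |
| 50 | 2.802/7.071 = 0.40 |
| 100 | 2.802/10 = 0.28 |

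For 21 people the noncentral t gives 0.64 rather than 0.61.

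**3. Why more people do not help attribution.** Suppose the model does nothing, the pre-post correlation is 0.5, and a village-wide shift of 0.2 SD arises from season, reporting or regression to the mean. All three inputs are assumptions. The SD of change is then √(2 × (1 − 0.5)) = 1 SD of the score and the standard error is 1/√m. The chance of a result significant at 5% is Φ(0.2√m − 1.96) + Φ(−0.2√m − 1.96):

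| m | 0.2 SD shift | Range over shifts of 0.1 to 0.3 SD |
|---|---|---|
| 21 | 15% | 7% to 28% |
| 50 | 29% | 11% to 56% |
| 100 | 52% | 17% to 85% |

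A larger pilot measures the total change more precisely, including the part unrelated to the model.

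**4. Rank, side by side.**

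| Item | As objective | As outcome |
|---|---|---|
| Function, quality of life, morbidity (Phase 1) | primary | primary |
| Feasibility and acceptability | secondary | secondary |
| Effectiveness of the model | not named in any objective | primary |

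Only the last row is out of line.

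**The case against.** The strongest reply is that effectiveness is not smuggled in. Objective 3 goes on to speak of improving functional ability and quality of life, and the abstract's Methods and the Phase 2 section name effectiveness openly beside feasibility. The primary item itself is defined modestly, as short-term change after the pilot. The text on scale-up is conditional, and policy impact is called a long-term goal. All of this is right. It shows that one item is ranked too high and labelled too strongly. It does not remove the mismatch or the confounding.

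Stronger readings are tempting and are not supported:

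- *The hierarchy is reversed.* Three of the four primary outcomes match the primary objective, so it is not.
- *Any improvement will be reported as proof and passed to policy.* That is conjecture about future reporting.
- *Regression to the mean alone would yield about a third of an SD.* Take the ICC implied by the design effect, 0.5/(20.8 − 1) = 0.025. The SD of village means is √(0.02525 + 0.97475/20.8) = 0.2685, and the worst of 25 lies about 1.964 × 0.2685 = 0.53 SD out. With reliability 0.02525/0.2685² = 0.35, regression is 0.65 × 0.53 = 0.34 SD. This holds only if the village is chosen as worst on Phase 1 scores, those scores serve as the pre-measure, and different people are measured afterwards. For the same people it is [1.964/(20.8 × 0.2685)] × (1 − r) = 0.352 × (1 − r), or 0.25 to 0.07 SD for an assumed test-retest r of 0.3 to 0.8. The article states none of these conditions, and Table 4 dates the pre-post measures to June to August 2027.
- *The village rule, the date of the pre-measure and the tools for mobility and self-rated health are defects.* A condensed article may leave these to the full protocol, so they are not raised.

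**Conclusion.** The point holds as a mismatch of rank and a limit on attribution. Effectiveness of the model is a primary outcome without a matching objective, and a single-village pre-post comparison cannot separate the model from time and place. That the evaluation is uncontrolled is inferred from every description of it; the article does not use the word.

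The conclusion rests on the stated design and needs no numerical assumption. The detectable changes of about 0.6, 0.4 and 0.3 SD, and the false-significance rates, are illustrations under assumed pilot sizes, correlation and shift. Validated is also too strong because the Feedback and refinement section plans to revise the model after the pilot, so the final version is not the one tested. The Phase 1 objectives and sample size are unaffected.

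**What to change.** 1. Move the fourth primary outcome to the secondary or exploratory outcomes and reword it as within-person change in function and quality of life after implementation. Report it as paired mean change with a 95% CI and no causal claim.
2. Make feasibility and acceptability the leading Phase 2 outcomes, in line with objective 3.
3. Replace effectiveness and validated with wording the design supports in the abstract (Methods and Expected Outcomes), the Phase 2 section, the section on assessing effectiveness, and Table 4, row 3. If the registry entry carries the same ranking, amend it too.

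The cost is a change of wording and a more modest claim for the pilot; no participants or fieldwork are added. On the stated timeline, implementation starts in June 2027, so the change can be made before any pilot data exist. If an effectiveness claim is wanted, the design would need comparator villages, more than one per arm, because one village per arm still confounds the model with village differences. That would be a larger study.

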#### Secondary outcomes.

Community Profiling: Mapping health determinants and identifying cultural beliefs or barriers to health-seeking behavior.Feasibility and Acceptability: Assessing how well the community-based integrated healthcare model is accepted by tribal residents and stakeholders.Healthcare Service Utilization: Measuring the community participation in health screenings and formal referral systems.Assessment of the feasibility, acceptability, and potential for wider implementation of the HOR-SATHI Healthy Ageing model in tribal communities.Institutional and Policy Impact: Long-term goals include the institutional adoption of the model by state health departments and providing evidence-based inputs for national geriatric and tribal health policies.

### Outcome measures and assessment timeline

#### Detailed data analysis.

A comprehensive statistical analysis plan for this study employs a multi-layered approach to address both quantitative and qualitative data strands, ensuring that the results are robust and account for the complexities of a tribal setting.

Quantitative Analysis Plan

Quantitative data will be processed and analysed using Jamovi statistical software.Descriptive Statistics: Continuous variables, including age, ADL/IADL scores, and WHOQOL-BREF scores, will be summarised using means, medians, and standard deviations.Categorical variables, including gender, tribal group, and chronic disease status, will be presented as frequencies and percentages.Bivariate Analysis: Chi-square tests will be used to assess associations between categorical variables, such as gender and functional decline.Comparison of Groups: Independent t-tests or ANOVA will be used to compare mean functional and quality-of-life scores across relevant groups, such as age categories and nutritional status.Correlation Analysis: Pearson’s or Spearman’s correlation coefficients will be used to examine relationships between functional status (ADL/IADL) and quality-of-life measures.

2. Qualitative Analysis Plan

The qualitative component will provide contextual insights to complement and interpret the quantitative findings through systematic coding and analysis.Thematic Analysis: Transcripts from In-Depth Interviews (IDIs), Focus Group Discussions (FGDs), and Key Informant Interviews (KIIs) will be systematically coded and analysed thematically to identify recurring patterns, cultural beliefs, healthcare experiences, and barriers to healthcare access. Transcripts will be coded and analysed using qualitative data management software such as NVivo, MAXQDA, or ATLAS.ti. Codes will be organized into broader themes addressing healthcare access, perceptions of ageing and functional decline, cultural practices, caregiving, and barriers to modern healthcare. Qualitative findings will initially be analysed independently and subsequently integrated with quantitative findings during interpretation to explain the contextual factors underlying the observed patterns.Software: Qualitative data coding and management will be supported using software such as NVivo, MAXQDA, or ATLAS.ti.Saturation: Data collection will continue until thematic saturation is achieved, with no emergence of substantially new themes or insights.Ensuring Qualitative Research QualityGeographical Coverage: Data collection across five blocks of East Singhbhum district will capture variation in experiences across the study area.Ethical Rigour: Transcripts will be anonymised and assigned unique identification codes, with audio recordings securely managed and accurately transcribed.Community Sensitisation: Village-level sensitisation meetings will be held prior to data collection to facilitate community engagement and encourage open participation.Thematic Saturation: Data collection will continue until no substantially new themes emerge. If new themes arise, additional interviews may be conducted, as permitted by the protocol.Triangulation: Use of IDIs, FGDs, and KIIs and inclusion of diverse stakeholder groups will strengthen the credibility and depth of findings.COREQ- A 32-item checklist designed to improve the transparency and reporting quality of qualitative studies will be employed.

3. Integration of Findings

The quantitative and qualitative data will be analysed independently and integrated at the interpretation stage.

Quantitative findings: Establish the prevalence and measurable patterns of functional decline, quality of life, and related health conditions.Qualitative findings: Provide contextual insights into the cultural, social, and healthcare-related factors underlying these findings.Integrated interpretation: The combined findings will directly inform the three-step healthcare model development process, beginning with domain identification and confirmation based on both quantitative evidence and qualitative themes.

4. Managing Confounding Factors

To minimize potential confounding, multivariable logistic regression models will be used to assess the independent associations with functional decline and quality of life.Adjustment for Confounders: Models will adjust for potential confounders, including age, gender, nutritional status, and the presence of chronic conditions.Stratification: Where appropriate, analyses will be stratified by gender to examine differences in health needs, occupational risks, and intervention-related outcomes between men and women.

5. Handling Missing Data

Prevention of Missing Data: Community sensitisation and support from Sahiya/ASHA workers will be used to strengthen community participation and minimise non-response.Management of Missing Values: The extent and pattern of missing data will be assessed. Where appropriate, suitable statistical methods, such as multiple imputation, may be considered during the final analysis to minimise potential bias.Data Cleaning and Anonymisation: Data will be systematically checked and cleaned before analysis. Unique identification codes will be used to maintain participant confidentiality and facilitate data management.

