### Sample size

#### Quantitative component.

The sample size was determined using Cochran’s formula for large populations, utilizing the reported 34.3% prevalence of functional disability among rural older adults from the Longitudinal Ageing Study in India (LASI) Wave 1 as the reference estimate [5].

This reference proportion (p) was applied alongside a 95% confidence level and a 5% margin of error to calculate an initial requirement of 346 participants. To account for the multistage cluster sampling design, a design effect of 1.5 was applied, resulting in a final target sample size of 520. The formula used here is as follows:

$$\begin{array}{c} n\;=\frac{\left(z^{\text{2}}*\;\hat{p}\left(\text{1}\;-\;\hat{p}\right)\right)}{\varepsilon^{\text{2}}}\;(\text{4}) \end{array}$$

where:

n = required sample sizeZ = 1.96 (95% confidence level)p = 0.343 (estimated prevalence of functional disability)1 − p = 0.657d = 0.05 (absolute precision)

Substituting these values:

n=(0.05)2(1.96)2×0.343×0.657=346

As the study will employ a multistage cluster sampling approach, a design effect (DEFF) of 1.5 was applied to account for clustering of observations. This yielded a final sample size of:

346 × 1.5 = 519

which was rounded to **520 participants.**

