### Sampling strategy

#### Quantitative component.

A multistage stratified random sampling strategy will be employed for the quantitative component. In the first stage, five tribal-dominated blocks of East Singhbhum district (Golmuri–Jugsalai, Potka, Ghatshila, Dhalbhumgarh, and Ghurabandha) will be included. In the second stage, five villages will be randomly selected from each block, resulting in a total of 25 study villages. The distribution of the sample across the five blocks and 25 selected villages is illustrated in Fig 2. Finally, eligible participants aged ≥45 years will be selected using proportionate allocation and systematic random sampling within each selected village until the required sample size is achieved Table 2–5.

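### The design effect of 1.5 used to size the Phase 1 survey is not carried into the analysis, so unadjusted prevalence intervals and tests of between-village factors would look more certain than they are

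*Protocol article*

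**What the plan says.** **Design.** Under Sample size (Quantitative component), the protocol article derives 346 participants for a single proportion and then states that "a design effect (DEFF) of 1.5 was applied to account for clustering of observations", which gives 519, rounded to 520. Under Sampling strategy, the five blocks are named and all are included, and "five villages will be randomly selected from each block, resulting in a total of 25 study villages". Participants are then "selected using proportionate allocation and systematic random sampling within each selected village".

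**Analysis.** The section Detailed data analysis, which presents itself as comprehensive, lists descriptive summaries and then three sets of methods:
- "Chi-square tests will be used to assess associations between categorical variables, such as gender and functional decline";
- "Independent t-tests or ANOVA will be used to compare mean functional and quality-of-life scores across relevant groups", with age category and nutritional status as examples;
- Pearson or Spearman correlations between functional status and quality of life.

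Under Managing Confounding Factors it adds that "multivariable logistic regression models will be used to assess the independent associations with functional decline and quality of life". The adjustment terms given are age, gender, nutritional status and chronic disease. Nothing in the article brings village, block, a cluster-adjusted variance or a random effect into the analysis.

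**The concern.** The sample was enlarged by half because people in the same village are expected to resemble one another. The named tests, in their standard form, treat all 520 people as independent. By the plan's own figure they carry the information of about 347. If the listed methods are followed as written, the extra participants recruited to pay for clustering are counted as extra information.

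Two results are exposed. One is the interval around the prevalence of functional disability, the quantity on which the study was sized. The other is any comparison of groups that differ mainly from village to village; tribal group, which the plan tabulates, could be such a variable. Functional decline and its risk factors are primary outcomes, and Phase 1 findings feed the choice of domains for the healthcare model.

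**Working it through.** **Inputs from the protocol article**
- Prevalence: "p = 0.343 (estimated prevalence of functional disability"), with z = 1.96 and absolute precision 0.05 (Sample size).
- Design effect (DEFF) 1.5 and N = 520 (Sample size).
- 25 villages in 5 blocks (Sampling strategy), so the mean number per village is m = 520/25 = 20.8.

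**Assumption.** No intraclass correlation (ICC) is stated. With equal village sizes, DEFF = 1 + (m − 1) × ICC, so DEFF 1.5 implies ICC = 0.5/19.8 = 0.025. Proportionate allocation may make village sizes unequal. That would change the implied ICC, but not the results below that use DEFF 1.5 directly.

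**1. The plan's figure reproduces.** n = 1.96² × 0.343 × 0.657 / 0.05² = 346.3, and 346 × 1.5 = 519, rounded to 520.

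**2. Prevalence interval at N = 520**
- Independence assumed: 1.96 × √(0.343 × 0.657 / 520) = 0.0408, or ±4.1 points.
- With DEFF 1.5: 0.0408 × √1.5 = 0.0500, or ±5.0 points. Effective sample size: 520/1.5 = 347.
- With DEFF 1.5 and t on 25 − 5 = 20 degrees of freedom (2.086 in place of 1.96): ±5.3 points.
- Ratio of unadjusted to adjusted width: 1/√1.5 = 0.816, so the unadjusted interval is 18% too narrow.
- Actual coverage of the unadjusted 95% interval: 2Φ(1.96/√1.5) − 1 = 0.890.

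**3. Type I error for a factor that varies only between villages.** The formula is 2[1 − Φ(1.96/√DEFF)].

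| ICC | DEFF | Type I error at nominal 5% |
|---|---|---|
| 0.01 (assumed) | 1.198 | 7.3% |
| 0.025 (implied by the plan) | 1.5 | 11.0% |
| 0.05 (assumed) | 1.99 | 16.5% |

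**4. How far this depends on the factor.** The unadjusted chi-square test was simulated with 25 villages, N = 520, prevalence 0.343, beta-binomial outcomes with ICC 0.025 and 20,000 runs per setting.

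| Factor tested | Type I error at nominal 5% |
|---|---|
| Varies only between villages | 11.1% |
| Partly clustered (assumed factor ICC 0.2) | 6.1% |
| Varies within villages, as gender does | 4.8% |

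The simulation agrees with the formula for the between-village case and shows no inflation for the within-village case. Only the chi-square test was simulated.

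**The case against.** The strongest reply is that little of what the plan names would go wrong. The example it gives for the chi-square test is gender, which varies within villages and keeps its nominal level. Age, nutritional status and chronic disease are also measured on individuals. Tribal group appears only among the variables to be tabulated, and block is named as an exposure in no test. This stands: a reader might infer that every Phase 1 p-value will be too small, and the documents do not support that. The 11% is the limit for a purely between-village factor.

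Three further points also limit the concern.
- A reader might infer that the ±5-point target is missed. It is not: 520 participants with DEFF 1.5 give ±5.0. Only an interval later computed without adjustment would be too narrow, and the analysis section names no interval method. Percentages and means are not biased merely because clustering is ignored.
- A reader might infer that false-positive risk factors pass straight into the Phase 2 model. No section makes a p-value the gate for a domain. Domains come from quantitative and qualitative findings together with the literature and existing frameworks, and stakeholders then refine the model.
- The need for sampling weights is a separate question about selection probabilities, and it is not shown here.

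It can also be said that a journal article may leave variance estimation to a fuller plan, and that the list of adjustment terms is not closed. That carries less weight. The article names particular tests, including t-tests explicitly for independent groups, and calls the plan comprehensive. Adding individual covariates to a regression does not correct its variance for clustering.

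**Conclusion.** The concern holds in limited form. The article assumes clustering when it sets the sample size and names analyses that, in their standard form, ignore it. That is an inconsistency between two stated choices rather than absent detail.

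At the plan's own design effect, the consequence is a prevalence interval 18% too narrow (±4.1 instead of ±5.0 points, about 89% coverage) and up to about 11% type I error for factors that vary mainly between villages. Partly clustered factors have a smaller inflation, and within-village contrasts have essentially none. The interval and the 11% rest on DEFF 1.5 being right. The range of about 7% to 16% rests on the assumed ICC of 0.01 to 0.05 and on equal village sizes.

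**What to change.** In Detailed data analysis and in Managing Confounding Factors, state that intervals for prevalences and means, group tests, correlations and regressions will account for village as the cluster and block as the stratum. Several methods are valid, and the plan should name the one it will use:
- design-based or cluster-robust standard errors, for example with a Rao-Scott chi-square test; or
- a village random intercept in the linear and logistic models.

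Add a small-sample correction for 25 villages, for example t on 20 degrees of freedom. Report the realised design effect beside the assumed 1.5. If the named package does not support the chosen method, name software that does.

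The cost is wording, a little analyst time and slightly wider reported intervals. No additional participants are needed, but each record must carry its village and block, which are the sampling units. The article schedules data collection to end by 15 September 2026 and analysis by 15 November 2026, so the change should be made before that analysis starts.
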